### Adverse events (AE)

Adverse events including toxicity and side effects should be reported according to Common Terminology Criteria for Adverse Events V3.0 (CTC AE) issued by National Cancer Institute (NCI) (http://ctep.cancer.gov/). All unexpected responses possibly or clearly related to the research will be reported. If serious adverse events (SAE) occur, experimental treatments will be stopped immediately and appropriate treatments will be offered. The type and frequency of adverse events will be reported for each group.

### Statistical analysis

All the clinical data will be saved in computers after collection work and database will be set up by Microsoft Access 2007 software. Statistical analysis will be conducted on an intention-to-treat basis with a 95% confidence interval using the SPSS 16.0 statistical package. For analysis of baseline characteristics, either two-sample t tests or Wilcoxon rank sum tests for continuous data and Chi-squared tests or Fisher’s exact tests for categorical data will be conducted after the test for normality. Kaplan-Meier survival analyses should be used for calculating median survival time (MST), Long-Rank is used between two groups. A significance level of 5% will be used throughout the analysis. Experts of Shanghai Medical Clinical Research Centre will be invited to manage the statistic analysis.

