## Background

Lung cancer is one of the most common malignant tumors in the world, accounting for 26–29% of all cancer deaths [1]. Increasingly, lung cancer is becoming a global health problem, with greater than 1 million deaths annually attributed to lung cancer [2]. Non-small cell lung cancer (NSCLC) accounts for approximately 80% of all lung cancer diagnoses and more than 75% of the patients are diagnosed at an advanced stage. Consequently, the prognosis for NSCLC continues to remain poor, with a 5-year survival of 15% [3].

At present, the high rate of recurrence and metastasis of postoperative non-small cell lung cancer (NSCLC) patients is one of the leading causes resulting in failure of treating lung cancer. More than 35% of postoperative lung cancer patients with stage I died in 5 years due to recurrence or metastasis; the 5-year survival rate of stage II, IIIa, IIIb was 31%, 17.9% and 11.7% respectively. The survival rate was improved by 5% with adjuvant chemotherapy after resection, so regimen consist of platinum-based two chemical medicines are commended as the adjuvant chemotherapy for treating postoperative NSCLC patients, but the toxicity and side effects of chemotherapy such as nausea and vomiting, hair loss, and bone-marrow depression can decrease quality of life (QOL) of patients [4-6]. These adverse reactions need to be treated, otherwise which will impact the completion of treatment. Literature and preliminary studies have shown that traditional Chinese medicine (TCM) can prolong survival and improve QOL, but high-level evidence is desperately needed to support this finding [7].

Over the past 10 years, many oncologists focused on survival advantage of adjuvant chemotherapy of postoperative non-small cell lung cancer patients. Data from JBR.10 study showed that overall QOL and functional domain scores are somewhat compromised after thoracotomy and pneumonectomy; but scores improve fairly early in patients who are not receiving chemotherapy [8]. As expected, adjuvant chemotherapy has an immediate negative impact on a number of aspects of QOL in individuals with NSCLC who have undergone resection with curative intent [9]. Chief among these is the symptoms that reflect most of the serious adverse effects associated with platinum-based chemotherapy: fatigue, loss of appetite, nausea, and vomiting. Therefore, QOL in clinical assessment has become more and more prominent in clinical research [10].

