### Study aims

The primary aim of this study is to evaluate the effectiveness of chemotherapy combined with or without TCM in QOL of postoperative NSCLC patients. The secondary aims are to compare the disease-free survival time (DFS), two-year disease-free survival rate and safety of intervention in the two groups.

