### Secondary outcome assessments

Two-year disease-free survival rate: the patients without recurrence and metastasis within 2 years after resection account for percentage of all patients.

Disease-free survival (DFS) :it refers to the interval time either from the first date of medication to that of recurrence and metastasis observed, or death for any reason (record according to the first event). The date of last evaluation will be recorded if patients either have no recurrence and metastasis when reach censored data, or loss of follow-up.

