## Discussion

The aim of this study is to prove that whether chemotherapy combined with TCM treatment can improve patients' quality of life and prolong survival. We have presented the design and protocol for a placebo-controlled, double-blinded RCT that will provide evidence for the effectiveness of chemotherapy combined with or without TCM in QOL of postoperative NSCLC patients. The result will provide support for integrative optimization of the treatment of lung cancer patients.

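### The statistical section applies Kaplan-Meier and log-rank to median survival time instead of DFS, does not use stage, and two-year DFS is a crude percentage with no handling of loss to follow-up

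*Protocol article*

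**What the plan says.** Study aims, in the protocol article, states: "The secondary aims are to compare the disease-free survival time (DFS), two-year disease-free survival rate and safety of intervention in the two groups".

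Secondary outcome assessments defines both survival outcomes:
- **Two-year DFS rate:** "the patients without recurrence and metastasis within 2 years after resection account for percentage of all patients".
- **DFS:** the interval "from the first date of medication to that of recurrence and metastasis observed, or death for any reason", whichever comes first. Patients without an event, or lost to follow-up, have the date of their last evaluation recorded.

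Statistical analysis has one sentence on time-to-event data: "Kaplan-Meier survival analyses should be used for calculating median survival time (MST), Long-Rank is used between two groups". The section also says that analysis is "on an intention-to-treat basis with a 95% confidence interval".

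The Discussion gives the trial's aim as showing whether adding TCM "can improve patients' quality of life and prolong survival". The Abstract, by contrast, expects an extension of disease-free survival.

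Randomization lists stage, pathological type, age and TCM syndrome as stratification factors. Sample size allows for 20% dropout.

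**The concern.** Three statements do not fit together.

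1. **The label.** Median survival time is not a defined outcome. The Background uses median survival in its usual sense, for earlier work in advanced disease. A reader of the Statistical analysis and Discussion sections could therefore expect an overall-survival comparison that the outcome sections do not contain. At reporting, this leaves room to choose between overall survival and DFS.
2. **Stage.** The test is described only as a comparison of two groups. Stage is balanced at randomisation and strongly related to outcome, but the stated comparison makes no use of it.
3. **The two-year rate.** It is a proportion of all patients, with no rule for those whose two-year status is unknown. Its event also differs from the DFS event, because death is left out.

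**Working it through.** The plan gives no event number, median, hazard ratio or power for DFS, so there is no figure of its own to reproduce. The checks below use its other figures.

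**1. Outcome against analysis**

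| Section | Quantity |
|---|---|
| Abstract | DFS, two-year DFS rate |
| Study aims | DFS, two-year DFS rate |
| Secondary outcome assessments | DFS, two-year DFS rate |
| Statistical analysis | median survival time |
| Discussion | prolonged survival |

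The last two rows match no defined outcome. DFS ends at the first event, so deaths after recurrence enter no endpoint.

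**2. How strongly stage matters**

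Inputs from the Background: more than 35% of stage I patients died within five years, so S(5) is below 0.65; and "the 5-year survival rate of stage II, IIIa, IIIb was 31%, 17.9% and 11.7% respectively". Eligible stages are Ib to IIIa. Assume a constant hazard, λ = −ln S(5)/5:
- Stage I: 0.4308/5 = 0.086 per year (a lower bound)
- Stage II: 1.1712/5 = 0.234 per year
- Stage IIIa: 1.7204/5 = 0.344 per year

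The ratio of IIIa to I is at most 1.7204/0.4308 = 3.99, and of II to I at most 1.1712/0.4308 = 2.72. The ratio of IIIa to II is 1.7204/1.1712 = 1.47. These are death hazards, and the stage I figure covers all of stage I, not Ib alone. They show that stage is prognostic; they do not give its effect on DFS.

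**3. What loss to follow-up can do to the crude percentage**

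Assume the 20% allowance also holds for two-year follow-up. The article does not say so, and its sample size is set for the three-month quality-of-life outcome. That is 0.20 × 240 = 48 patients per arm. Take the extreme case in which all leave early, without an event and independently of prognosis. Let p be the true two-year proportion:
- lost patients counted as recurrence-free: 0.8p + 0.2
- lost patients counted as failures: 0.8p

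The gap is 20 percentage points for any p. With equal loss and the same rule in both arms, the difference becomes 0.8 × (p₁ − p₀), one fifth smaller than the true difference. With less or later loss both effects shrink, to zero if nobody is lost. Kaplan-Meier uses each patient's follow-up up to censoring and is unbiased if loss is unrelated to prognosis.

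**4. Event and origin**

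Read literally, a patient who dies within two years without recurrence counts as a success in the rate but as an event in DFS. The rate runs from resection and DFS from first medication. The inclusion criteria allow up to six weeks between operation and first chemotherapy.

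**5. Would the median be reached?**

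Overall survival, constant hazard, S(2) = S(5)^(2/5) and median = 5 ln 2/(−ln S(5)):

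| Stage | S(2) | Median, years |
|---|---|---|
| I | at most 0.842 | at most 8.05 |
| II | 0.626 | 2.96 |
| IIIa | 0.503 | 2.01 |

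A front-loaded hazard (Weibull shape 0.8) gives 0.179^(0.4^0.8) = 0.179^0.480 = 0.438 for IIIa, so the median then falls before two years.

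For DFS, assume a hazard 1.5 times the death hazard and solve Σ w·S(5)^(1.5t/5) = 0.5 over assumed stage mixes:

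| I / II / IIIa mix | Median DFS, years |
|---|---|
| all IIIa | 1.34 |
| 0 / 50 / 50 | 1.62 |
| 20 / 30 / 50 | 1.89 |
| equal thirds | 2.28 |
| 50 / 25 / 25 | 2.81 |

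Median DFS falls on either side of two years, depending on inputs the article does not give.

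**The case against.** The strongest defence is that DFS is the only time-to-event outcome in the article, so the Kaplan-Meier and log-rank sentence can only be meant for DFS, and median survival time is loose wording. The Discussion phrase is likewise loose prose on which no analysis depends. This largely stands and is why the point is minor. It does not remove the mismatch, because the wrong quantity is named in the section that governs the analysis.

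A second defence is that hazard ratios, Cox models and stratified tests are details an article may leave to a full protocol or SAP. This also stands: their absence is not an error, and silence on stage is not a decision to ignore it. An unstratified log-rank test remains valid after stratified randomisation. Stratifying by stage is an improvement to a stated method, not the repair of an invalid one.

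A reader might go further and infer three things that the documents do not support:
- **That median survival time is the only survival summary.** The two-year DFS rate is also a defined outcome to be compared between groups.
- **That DFS therefore gets no effect estimate.** A two-year rate compared between arms, with the stated 95% confidence interval, is one, and a hazard ratio may be specified elsewhere.
- **That the median would not be reached at two years on the article's own rates.** Those are five-year overall-survival rates. The inference needs a constant hazard and a two-year data cut-off, which is not stated, and it cannot be derived for DFS. If the two years in Sample size are the accrual period and every patient is followed for two years, the earliest patients would have about four years of follow-up.

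**Conclusion.** The point holds as a minor one on secondary outcomes. The Statistical analysis section names a quantity that is not an outcome, and no defined endpoint supports the Discussion's survival aim; neither statement depends on an assumption.

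The case for using stage rests on the Randomization section and the Background's survival rates (hazard ratio of at most about 4 across the eligible range, under constant hazard). The case against the crude percentage rests on its definition. The 20-point figure is an upper bound that assumes 20% early, event-free loss by two years, which the article does not state for DFS. The primary quality-of-life comparison is untouched.

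**What to change.** - **Statistical analysis:** replace median survival time with DFS as the Kaplan-Meier and log-rank endpoint. Stratify the log-rank test by stage, and add a matching Cox hazard ratio with 95% CI using the randomisation factors (stage, pathological type, age, TCM syndrome).
- **Secondary outcome assessments:** replace the crude percentage with the Kaplan-Meier two-year DFS estimate per arm and its 95% CI. Use the DFS event definition (recurrence, metastasis or death) and its rule for patients without an event or lost. State one time origin for both outcomes.
- **Discussion:** say disease-free survival instead of survival.

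The cost is wording and a little extra analysis. The dates needed are those the DFS definition already requires, so no patients or visits are added.

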## Discussion

The aim of this study is to prove that whether chemotherapy combined with TCM treatment can improve patients' quality of life and prolong survival. We have presented the design and protocol for a placebo-controlled, double-blinded RCT that will provide evidence for the effectiveness of chemotherapy combined with or without TCM in QOL of postoperative NSCLC patients. The result will provide support for integrative optimization of the treatment of lung cancer patients.
